In PTSD, enhanced HPA-axis feedback regulation can lead to exaggerated suppression of cortisol, which results in lower circulating cortisol levels (Goenjian et al., 1996; Grossman et al., 2003; Pitman et al., 2012; Stein et al., 1997; Yehuda, 2009; Yehuda et al., 1993, 1995, 2002, 2004). Although most meta-analyses support this notion of HPA-axis dysregulation (Meewisse et al., 2007; Morris et al., 2012; Pan et al., 2018), another meta-analysis (Klaassens et al., 2012) and multiple studies that failed to replicate these findings suggest that low cortisol may only be observed under certain conditions, perhaps only within subgroups of individuals with PTSD (Meewisse et al., 2007; Pitman et al., 2012; Zoladz & Diamond, 2013). DNA methylation can suppress gene transcription and, as such, contribute to individual differences in glucocorticoid signalling (Turecki & Meaney, 2016; Zhang et al., 2013). Previous research indicated that decreased methylation of the glucocorticoid receptor (GR) gene *NR3C1* is associated with ELA (Oberlander et al., 2008; Parent et al., 2018; Weaver et al., 2007). Moreover, allele-specific DNA demethylation of *FKBP5* (a co-chaperone that regulates GR activity) mediates gene-by-ELA interactions and induces long-term HPA-axis dysregulation (Klengel et al., 2013; Koenig et al., 2018; Mehta et al., 2011). HPA-axis dysregulation and methylation status of *NR3C1* and *FKBP5* are also associated with increased lifetime risk for PTSD development if exposed to traumatic events (Labonté et al., 2014; van Zuiden et al., 2011; Vukojevic et al., 2014; Yehuda et al., 2015b). Beyond these observational findings, experimental research with rodents has provided causal support that ELA can lead to HPA-axis dysregulation. ELA was shown to cause lower glucocorticoid levels, which was accompanied by an upregulation of GRs within the hippocampus and medial prefrontal cortex and decreased later-life social behaviour, of which the latter was reinstated with glucocorticoid administration (Perry et al., 2019). Gene expression patterns thus tune the sensitivity of the stress response and negative feedback inhibition via epigenetic mechanisms.

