Collectively, the aforementioned findings suggest a mechanistic model in which PTSD patients with dysfunctions in glucocorticoid signalling – potentially emerging from epigenetic programming by ELA – insufficiently benefit from PTSD treatments. This group of non-responding and relapsing individuals could potentially benefit from exogenous glucocorticoid administration during extinction learning (De Quervain et al., 2019). The current study integrates an observational study with a pharmacological intervention and functional resonance imaging (fMRI) study to provide a translational effort towards improved and personalized PTSD treatment. In our observational study, we investigate interaction effects of ELA and epigenetic programming of glucocorticoid signalling on HPA-axis regulation and their association with treatment outcome in a group of individuals with PTSD. The pharmacological intervention and fMRI study investigates glucocorticoid-induced enhancement of extinction learning in PTSD patients in a placebo-controlled clinical trial with a crossover design. By leveraging an experimental fear conditioning and extinction task within a virtual environment that uses houses as spatial contexts for the experiences, we will be able to investigate the effect of exogenous glucocorticoids on the context dependency of fear and extinction memories. Overall, we aim to provide proof of concept that HPA-axis dysregulation in individuals with PTSD is related to ELA and associated epigenetic markers of glucocorticoid signalling; that these individuals with PTSD show impairments in extinction learning and altered neural responses; and that this subgroup would particularly benefit from glucocorticoid augmentation of extinction learning through a mechanism of enhancing the strength and generalization of extinction memories.

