### Population

2.2.

This study aims to include *n *= 160 people with PTSD (part A), half of whom participate in the entire study (*n = *80 for part B). In addition, *n *= 30 control group participants are recruited (part A). All participants must be aged 18–64 years old. Exclusion criteria for both groups are listed in Table 1. More details on criteria assessed during the screening visit and amendments during the trial are listed in the Supplementary Material (S1 and S2). Power calculations are also described in the Supplementary Material (S3).

**Table 1. T0001:** Exclusion criteria.

Group	Exclusion criteria
PTSD	General exclusion criteria:
	- Current psychotic or manic episode
	- Benzodiazepine medication: Daily intake of benzodiazepines, or otherwise irregular intake of benzodiazepines (‘when needed’) but unable to withhold intake according to study procedures Exception: low evening doses (sleep medication)
	- For part B only: MRI contraindications
	Criteria assessed during screening session:
	- Does not receive a classification of current PTSD according to clinical interview assessment
Control	General exclusion criteria:
	- Current or past psychiatric disorder
	- Use of psychotropic medication
	- History of childhood maltreatment
	Criteria assessed during screening session:
	- Early-life adversity according to questionnaire assessment
	- (History of) psychiatric disorders according to clinical interview assessment
Both	General exclusion criteria:
	- General learning disability or intellectual disability
	- Body mass index > 35 kg/m^2^
	- Pregnancy or breastfeeding
	- Substance use: Unable or unwilling to withhold recreational drug use and limit alcohol use according to study procedures
	- Nicotine smoking: Unable or unwilling to discuss frequency and timing of smoking according to study procedures
	- Glucocorticoid medication/supplements: Current or recent regular use of systemic corticosteroids (< 1 month ago). For non-systemic corticosteroids, average use of more than once a week and/or no possibility to withhold according to study procedures
	- Hypersensitivity to glucocorticoids
	Criteria only if relevant to study outcomes or feasibility of study procedures:
	- Relevant neurological disorder
	- Severe physical disorder
	- Relevant endocrine disease and/or current or recent endocrine treatment

Note: MRI = magnetic resonance imaging; PTSD = post-traumatic stress disorder; BMI = body mass index.

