As a validation check of the proposed epigenetic mechanism, it will first be ascertained that for both genes *NR3C1* and *FKBP5* (and potentially other genes of interest), DNA methylation inversely correlates with mRNA levels in the blood. This will be tested with Pearson or Spearman correlation tests. Linear regression models will then investigate the associations between ELA and DNA methylation at *NR3C1* and *FKBP5* in the PTSD group, with the inclusion of age and gender as covariates. For *FKBP5*, we will take into account polymorphisms of SNP rs1360780 (minor risk allele T versus homozygous C-allele carriers) by specification of an ELA-by-genotype interaction effect, because of previously reported allele-specific gene–childhood effects (Klengel et al., 2013). FDR correction will be applied over the number of regression models with different DNA methylation outcome variables and/or different ELA predictor variables. The association between DNA methylation status and HPA-axis dysregulation will also be investigated with linear regression models, with the inclusion of age and gender as covariates. FDR correction will be applied over the number of regression models with different HPA-axis dysregulation outcome variables and/or different DNA methylation predictor variables. Additional linear regression models will explore additional covariates, such as other relevant task variables (e.g. SECPT stress ratings, duration), lifestyle factors (smoking, alcohol use, and drug use), concurrent psychiatric symptoms, and (female) menstrual cycle. If appropriate, regression models will be followed up by mediation models to directly test mediation of the association between ELA and HPA-axis dysregulation by methylation status of glucocorticoid-related genes.
4.Exploratively, investigate whether HPA-axis dysregulation and glucocorticoid signalling are associated with treatment response.

In the PTSD group, functional markers of HPA-axis dysregulation associated with treatment response will be examined with mixed-effects linear regression models. Since the PTSD group will have experienced heterogeneous courses of treatment, a specific analysis plan will be drafted after exploration of the frequency and variety of treatments within the sample.

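### FKBP5 genotype is in the ELA-to-methylation model but not in the stated methylation-to-HPA model, so that second path can be confounded by the risk allele

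*Protocol article*

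**What the plan says.** Objective 3 is set out in the protocol article, section 2.6.1.2 (observational study), in three steps.

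- **ELA to methylation.** "Linear regression models will then investigate the associations between ELA and DNA methylation at *NR3C1* and *FKBP5* in the PTSD group", adjusted for age and gender. For FKBP5 the plan accounts for rs1360780 (T carriers against C homozygotes) "by specification of an ELA-by-genotype interaction effect", because allele-specific effects have been reported before.
- **Methylation to HPA axis.** Two covariates are named: "association between DNA methylation status and HPA-axis dysregulation will also be investigated with linear regression models, with the inclusion of age and gender". Further exploratory covariates follow: task variables, lifestyle, psychiatric symptoms and menstrual cycle. Genotype is not among the examples, though the list is open.
- **Mediation.** If appropriate, the regressions are to be "followed up by mediation models to directly test mediation of the association between ELA and HPA-axis dysregulation by methylation status of glucocorticoid-related genes". No covariates or moderators are named.

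Section 2.6.1.1 adds in general terms that genotype interactions will be assessed, without naming a model. The Introduction says that allele-specific FKBP5 demethylation "mediates gene-by-ELA interactions and induces long-term HPA-axis dysregulation".

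**The concern.** The plan's own rationale gives the FKBP5 allele a role along the whole chain, from adversity through methylation to HPA-axis feedback. Yet the explicit genotype term stops after the first link. In the second link the allele is a candidate common cause: it may shift methylation, and it may shift HPA feedback by routes other than the methylation measured. A regression adjusted for age and gender alone would then credit methylation with part of the allele's effect.

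Objective 3 asks whether methylation mediates the ELA–HPA association, so a spurious second path would count as support for the mechanism. The planned FDR correction does not help, because it controls multiplicity and not bias. The point concerns FKBP5 only; no genotype term is specified for NR3C1.

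**Working it through.** **Inputs from the documents.** The planned PTSD group in part A is 160 (section 2.2). The covariates are as listed above. The article states no power, effect size or significance level for this objective; power calculations are referred to Supplementary Material S3, which is not shown. There is therefore no figure of the plan's to reproduce.

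**Assumptions.** Carrier share p = 0.5. ELA is standardised and acts on methylation in carriers only, with slope a = 0.4. Genotype shifts methylation by gM and the HPA outcome by gY, in residual SD units. The true methylation effect is b = 0, and residual SDs are 1. Tests are two-sided at 5% without FDR correction, with 4000 simulated samples per scenario.

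**Bias when genotype is omitted.**

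bias in b = p(1 − p)·gM·gY / Var(M), where Var(M) = 1 + a²p + gM²·p(1 − p) = 1.08 + 0.25·gM²

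| gM | gY | Bias in b | False positives, genotype omitted |
|---|---|---|---|
| 0.2 | 0.2 | 0.010/1.090 = 0.009 | about 5% |
| 0.3 | 0.3 | 0.0225/1.1025 = 0.020 | about 6% |
| 0.5 | 0.3 | 0.0375/1.1425 = 0.033 | about 7% |
| 0.8 | 0.3 | 0.060/1.240 = 0.048 | about 10% |
| 0.5 | 0.5 | 0.0625/1.1425 = 0.055 | about 11% |
| 0.8 | 0.5 | 0.100/1.240 = 0.081 | about 19–20% |

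With genotype in the model the bias is about 0 and the rejection rate about 5% in every row. Shifts in opposite directions give the same bias with the sign reversed. At an extreme of 0.8 SD on both variables, the rate without genotype is about 40%.

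**Is the second path also diluted?** With b = 0.3 in everyone and no genotype shifts, the estimated slope is 0.30 with and without genotype. Dilution of this slope would require the slope itself to differ by allele, which section 2.6.1.2 does not state.

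**Power of the two regressions as written.** With a = 0.4 in carriers, b = 0.3 and p = 0.5, power is the chance that both paths are significant, testing the carrier slope in the first path:

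- genotype in the first path only, as stated: about 91%;
- genotype in both paths: about 90%;
- genotype in neither path: about 65–67%.

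**What if a mediation model dropped genotype?** The pooled indirect effect would be p·a·b, against a·b = 0.4 × 0.3 = 0.12 in carriers. At carrier shares of 40%, 50% and 60% this gives 0.048, 0.060 and 0.072. The simulation returns 0.047, 0.059 and 0.072.

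**The case against.** The strongest reply is that the problem is conditional and may be small. Confounding needs the allele to shift both variables, and the documents give no figures for either shift. At 0.2–0.3 SD each, the error rate is essentially nominal. The exploratory covariate list is open, section 2.6.1.1 promises genotype interactions, and a condensed article may leave detail to the full protocol. All of this limits the size of the point. It does not put genotype into the methylation-to-HPA model, whose covariates the article does state.

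Three stronger readings may tempt a reader, and the documents support none of them.

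- **That the plan averages the allele-specific effect over non-carriers.** The first regression contains the ELA-by-genotype term. The mediation sentence is conditional and neither includes nor excludes genotype. Since it follows up models that contain the interaction, a moderated mediation is a natural reading.
- **That the plan loses power, at about 65% against 90%.** The lower figure belongs to an analysis with genotype in neither path, which is not what section 2.6.1.2 describes. The stated regressions and the full-genotype version have practically the same power.
- **That an announced aim cannot be answered.** The Introduction says "we investigate interaction effects of ELA and epigenetic programming of glucocorticoid signalling on HPA-axis regulation", and no HPA model has an ELA-by-methylation term. But this is introductory wording. The formal objectives in section 1.1 ask about association and mediation, and the analyses match them.

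**Conclusion.** The point holds in a limited form. For FKBP5, the stated methylation-to-HPA regression omits a genotype that the plan itself treats as part of the pathway, so its coefficient can be confounded. Under the assumptions above, false positives run from about 5–6% (0.2–0.3 SD on each variable) to about 7–20% (0.5–0.8 SD in methylation with 0.3–0.5 SD in the HPA outcome), against about 5% with genotype included. Where in that range the trial would fall cannot be derived from the documents.

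Shrinkage of the carriers' indirect effect, roughly to the carrier share of its size, would follow only if the mediation model were fitted without genotype, and the plan does not say that it will be. The remedy is worth making because it is nearly free, not because serious bias has been shown.

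**What to change.** In section 2.6.1.2, objective 3:

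1. Add rs1360780 genotype (T carriers against C homozygotes) as a covariate, with age and gender, to every FKBP5 methylation-to-HPA regression.
2. State that any FKBP5 mediation model carries genotype and the already specified ELA-by-genotype term, and that the indirect effect is reported separately for T carriers and C homozygotes with a bootstrap interval.

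Genotyping is already planned from the blood sample (section 2.4.2.2), so no new data are needed. The cost is one or two degrees of freedom per model out of 160 patients, and genotype-specific intervals that are wider than a pooled one.

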#### Pharmacological intervention and fMRI study

2.6.2.

##### Primary outcome measures

2.6.2.1.

Successful fear acquisition, as indicated by a higher SER for the CS+s in comparison to CS− in the last block of the fear acquisition task, is a prerequisite for the assessment of extinction learning. During the fear extinction task, fear extinction should be indicated by decreasing SER, showing no expectancy of shock in the last block of this task. Fear acquisition and fear extinction will also be signalled by psychophysiological outcome measures (SCR and PDR). Neuroimaging during the fear extinction task investigates pharmacological effects on neural responses associated with fear extinction learning. Ultimately, the strength and generalization of the fear and extinction memories are assessed in the extinction recall task during recall of these memories upon presentation of the CSs in different contexts. Here, the primary outcome variables are SCR, PDR, and SER. Details of psychophysiological analyses are described in Supplementary Material S13. More specifically, increased strength of extinction memory should be indicated by smaller differential responses within the extinction context, whereas increased generalization of extinction memory should be indicated by a context interaction effect showing transfer of extinction to novel and/or acquisition contexts. In addition, effects of HPA-axis dysregulation are investigated to investigate their role in glucocorticoid effects on extinction recall. Relative suppression of the CAR from the DST is prespecified as the primary outcome measure, and based on a median split, the PTSD group will be divided over two subgroups. Grouping based on other HPA-axis outcome variables will be regarded as secondary and subjected to appropriate multiple-comparison corrections. Planned MRI (preprocessing) analyses are discussed in the Supplementary Material (S14).

##### Statistical modelling

2.6.2.2.

1. Investigate whether patients with HPA-axis dysregulation show impairments in extinction learning relative to patients without HPA-axis dysregulation, and whether this is accompanied by different neural responses during extinction learning in brain regions associated with fear expression and extinction.

This objective will be investigated with data from placebo sessions only. At the psychophysiological level, we expect HPA-axis dysregulation to be associated with lower strength of the extinction memory, indicated by lower differential responses for CS+U vs CS+E and/or higher differential responses for CS+E vs CS− during the extinction recall task. This will be modelled with a two-way ANOVA of averaged differential responses during the first block, which is within the extinction context and contains two presentations of each CS. Higher generalization of the extinction memory for the HPA-axis normalized group would be indicated by a context interaction effect that shows less renewal of fear, i.e. a lower increase of differential effects upon stimulus presentations within the novel and acquisition contexts. These comparisons may be affected by an overall attenuation of fear responses due to re-extinction over the course of the extinction recall task. This effect will be investigated with a 2 (group) by 3 (context) mixed ANOVA of averaged differential responses during the first block of each context. Both models will include the covariate order of medication administration, and, if appropriate, the covariates age and gender. Outcome measures SCR, PDR, and SER will be included in separate models, but since these measures of conditioning are complementary, no multiple comparisons correction will be applied. At the level of neuroimaging, differences in extinction learning signalled during the fear extinction task could be underlying the differences at the behavioural level. Here, we would expect different neural responses in brain regions and networks associated with (context-dependent) extinction learning for patients with HPA-axis dysregulation, which could also be associated with less successful recall of the extinction memory.

2. Investigate whether the subgroup of PTSD patients with HPA-axis dysregulation particularly benefits from hydrocortisone administration (versus placebo) to improve the strength and generalization of extinction memories.

To answer the main objective of the pharmacological intervention study, the aforementioned psychophysiological models will be extended with data from the hydrocortisone sessions (thus adding a within-subjects category for medication). Period effects may follow from the crossover design and will be accounted for by defining a medication-by-order interaction effect. Based on previous research, we hypothesize a group-by-medication interaction effect, indicating greater strength and/or generalization of the extinction memory following administration of hydrocortisone, that is most pronounced for the HPA-axis dysregulation group.

3. Investigate underlying neural mechanisms of glucocorticoid administration (versus placebo) to improve extinction learning.

Recruitment of neural networks associated with (context-dependent) extinction learning for patients with HPA-axis dysregulation (see point 1 above) would be expected to enhance following hydrocortisone administration. Pharmacological effects and their potential interactions with HPA-axis dysregulation are primarily investigated during the extinction learning task, but will also be supported by the following analyses: (1) amygdala (and salience network) reactivity to the emotion processing task, which we expect to be reduced after hydrocortisone administration; and (2) resting-state connectivity in networks associated with (context-dependent) extinction learning – ventromedial prefrontal cortex–amygdala connectivity, in particular – which we expect to be enhanced after hydrocortisone administration.

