## Abstract

**Background:** Trauma-focused treatments for post-traumatic stress disorder (PTSD) are effective for many patients. However, relapse may occur when acquired extinction memories fail to generalize beyond treatment contexts. A subgroup of PTSD patients – potentially with substantial exposure to early-life adversity (ELA) – show dysregulation of the hypothalamic–pituitary–adrenal (HPA) axis, which results in lower cortisol levels. Glucocorticoids, including cortisol, appear to facilitate strength and generalization of emotional memories.

**Objective:** We describe the protocol of an integrated PTSD study. We investigate (A) associations between HPA-axis dysregulation, ELA, epigenetic markers, and PTSD treatment outcome (observational study); and (B) effects of exogenous glucocorticoids on strength and generalization of extinction memories and associated neural mechanisms [pharmacological intervention study with functional magnetic resonance imaging (fMRI)]. The objective is to provide proof of concept that PTSD patients with HPA-axis dysregulation often experienced ELA and may show improved strength and generalization of extinction learning after glucocorticoid administration.

**Method:** The observational study (*n *= 160 PTSD group, *n *= 30 control group) assesses ELA, follow-up PTSD symptoms, epigenetic markers, and HPA-axis characteristics (salivary cortisol levels during low-dose dexamethasone suppression test and socially evaluated cold-pressor test). The pharmacological intervention study (*n *= 80 PTSD group, with and without HPA-axis dysregulation) is a placebo-controlled fMRI study with a crossover design. To investigate strength and generalization of extinction memories, we use a differential fear acquisition, extinction, and extinction recall task with spatial contexts within a virtual environment. Prior to extinction learning, 20 mg hydrocortisone or placebo is administered. During next-day recall, strength of the extinction memory is determined by recovery of skin conductance and pupil dilation differential responding, whereas generalization is assessed by comparing responses between different spatial contexts.

**Conclusion:** The integrated study described in the current protocol paper could inform a personalized treatment approach in which these PTSD patients may receive glucocorticoids as a treatment enhancer in trauma-focused therapies.

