**Figure 2. F0002:**
[figure not shown]
Fear conditioning and extinction task. (a) The task consists of a fear acquisition, fear extinction, and extinction recall task. In this study, hydrocortisone or placebo is administered 45–55 minutes prior to the fear extinction task. This fear extinction task is completed during functional magnetic resonance imaging (fMRI) scanning. Outcome measures are psychophysiological measurements (pupil, skin conductance) and shock expectancy ratings during all tasks, and neuroimaging during the fear extinction task. (b) To accommodate the crossover design of this study, the task has two virtual environments (nature and city environment) with three houses each. These houses function as occasion setters, i.e., ‘contexts’ for the experiences (acquisition, extinction, novel). (c) Task procedures to start a task block. The participant is first instructed to enter a booth. Inside this booth, they are presented with the house to which they should navigate. They should also rate on a five-point scale whether they expect to receive at least one shock within that house in the upcoming block. Entering a booth within the correct house triggers the start of a block. (d) Task procedures within a block, per trial. The participant is presented with a fixation cross before presentation of a conditioned stimulus (CS). During CS presentation, they should rate on a five-point scale whether they expect to receive a shock based on the stimulus that is being presented. At the end of stimulus presentation, depending on the task and trial, negative reinforcement with an electric shock to the fingers may follow. (e) Two sets of three shapes that function as CSs within the paradigm.

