##### Task phases

2.4.5.1.

*Fear acquisition.* Three different CSs are presented in four blocks. Each block consists of four trials per CS, totalling to 12 trials per block. One CS is never followed by shock (CS−), whereas two other CSs (CS+s) are sometimes followed by shock according to a 50% reinforcement schedule. All blocks are completed within the same house; this house is established as the ‘acquisition context’.*Fear extinction.* The CS− and one of the two CS+s are presented in four blocks. Each block consists of four trials per CS, totalling to eight trials per block. Here, the included CS+ is being extinguished (CS+E) as no shocks are administered during this phase. The CS+ that is omitted from this phase remains unextinguished (CS+U). All blocks are completed within the same house, differently from the fear acquisition phase; this house is established as the ‘extinction context’.*Extinction recall.* All three CSs (CS+E, CS+U, and CS−) are presented in six blocks. Each block consists of two trials per CS, totalling to six trials per block. The first two blocks are presented within the ‘extinction context' house, the next two blocks within the ‘novel context' house, and the last two blocks within the ‘acquisition context' house.

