**Figure 3. F0003:**
[figure not shown]
Timeline of study procedures per session in the pharmacological intervention and functional magnetic resonance imaging (fMRI) study. The first study visit typically starts around 10 or 11 a.m. (10:00 or 11:00 h), and the next-day visit typically starts around 3.15 or 4.15 p.m. (15:15 or 16:15 h).

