##### MRI visit (B1.1 and B2.1)

2.5.5.1.

In the psychophysiology laboratory, the participant completes the two practice tasks (see Section 2.4.5) in the presence of the researcher. If more practice is needed, a practice test is repeated. The intensity of electric shocks is determined by a calibration procedure (for details, see Supplementary Material S9). The participant then performs the fear acquisition task with psychophysiological assessment (pupil, skin conductance, heart rate). After a lunch break, the participant completes several online questionnaires, followed by a practice session in the dummy MRI laboratory and a second break. Subsequently, they provide a baseline saliva sample, which is followed by the oral intake of the study medication (indistinguishable capsule with 20 mg hydrocortisone or placebo). During the experimental set-up for the MRI session, the participant provides another saliva sample 30 minutes after medication administration. Heart rate and respiratory data are collected throughout the MRI session. The first part of the MRI session consists of a field map and task-based fMRI during fear extinction (45–55 minutes after medication administration) with psychophysiological assessment (pupil, skin conductance, heart rate). This is followed by a structural scan (T1-weighted during the first session; diffusion tensor imaging during the second session). During a short break, another saliva sample is provided (60–75 minutes after medication administration). The second part of the MRI session consists of resting-state fMRI with field mapping, and task-based fMRI during emotion processing with field mapping.

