##### Next-day visit (B1.2 and B2.2)

2.5.5.2.

The participant completes online questionnaires and returns to the psychophysiology laboratory to complete the extinction recall task with psychophysiological assessment (pupil, skin conductance, heart rate). This visit is always scheduled the next day in the late afternoon, with an interval of at least 24 hours between the start of the fear extinction task and extinction recall task.

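### A fear memory strengthened by hydrocortisone could be read as stronger extinction, because CS+U vs CS+E may count alone and the article names no CS+U vs CS− contrast

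*Protocol article*

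**What the plan says.** **Timing.** Section 2.5.5.1 puts fear acquisition first in the MRI visit. Then: "After a lunch break, the participant completes several online questionnaires, followed by a practice session in the dummy MRI laboratory and a second break". Next: "Subsequently, they provide a baseline saliva sample, which is followed by the oral intake of the study medication". The Figure 2 caption adds that "hydrocortisone or placebo is administered 45–55 minutes prior to the fear extinction task". Recall is on the following day, "with an interval of at least 24 hours between the start of the fear extinction task and extinction recall task" (section 2.5.5.2).

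**Stimuli.** Under section 2.4.5.1, two CS+s are acquired. One is extinguished (CS+E), the other is left out of extinction (CS+U), and both are shown at recall with the CS−.

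**Contrasts.** For objective 1 (placebo sessions only), section 2.6.2.2 takes a weaker extinction memory to be "indicated by lower differential responses for CS+U vs CS+E and/or higher differential responses" for CS+E vs CS−. No CS+U vs CS− contrast is named. Objective 2 adds a within-subject medication factor to these models and hypothesises a group-by-medication interaction.

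**Premise.** The Abstract states: "Glucocorticoids, including cortisol, appear to facilitate strength and generalization of emotional memories". Section 2.6.2.1 lists fear memory, alongside extinction memory, among the things recall assesses.

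**The concern.** In placebo sessions no drug acts on CS+U, so it is a reasonable reference for CS+E. Once the model compares hydrocortisone with placebo, CS+U is no longer a fixed reference. It was learned hours before dosing, is never extinguished, and is tested after the drug has had a night in which to affect memory. The article's own premise covers emotional memories generally, not only safety memories, so a drug effect on CS+U is plausible on the article's terms.

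A rise in CS+U vs CS+E can come from a lower CS+E (better extinction) or from a higher CS+U (stronger fear). The and/or wording lets the contrast count without the other one agreeing. Objective 2 is the main question of part B, and the Conclusion would use a positive answer to support hydrocortisone as a treatment enhancer. Reading stronger fear as stronger extinction would reverse the meaning of that result.

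**Working it through.** The article gives no effect size, SD or alpha for these contrasts (power is in Supplement S3, not shown), so there is no figure of the plan to reproduce. The values below are illustrative assumptions, except n = 80 and the clock times.

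**1. Could the drug reach the fear memory?** The Figure 3 caption gives visit starts of about 10:00 or 11:00 and next-day starts of about 15:15 or 16:15. Pair the early times with each other and the late times with each other, and assume recall begins 0–30 min into the next-day visit. For a 10:00 start, the 24-hour rule puts the start of extinction no later than 15:15–15:45. Subtracting 45–55 min puts dosing no later than 14:20–15:00, which is about 4.3–5.0 h after the visit starts. The 11:00 start gives the same interval. Dosing a few hours after acquisition is thus a fair inference, though not a stated figure.

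**2. What each explanation does to the contrasts.** Set CS− = 0 and, under placebo, CS+U = 1 and CS+E = 1 − x, where x is the fraction suppressed by extinction. Let g be a drug gain in fear memory. With x = 0.5, placebo gives CS+U−CS+E = 0.50, CS+E−CS− = 0.50 and CS+U−CS− = 1.00. Changes under hydrocortisone:

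| Scenario | CS+U−CS+E | CS+E−CS− | CS+U−CS− |
|---|---|---|---|
| True benefit: x from 0.5 to 0.7, g = 0 | +0.20 | −0.20 | 0 |
| Proportional fear gain, g = 0.4 | +0.20 | +0.20 | +0.40 |
| Gain in CS+U only, g = 0.2 | +0.20 | 0 | +0.20 |
| Equal additive gain in both CS+s, g = 0.4 | 0 | +0.40 | +0.40 |

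The first three rows cannot be told apart on CS+U vs CS+E. Under proportional gain the shift is g·x. For g = 0.4 it is 0 at x = 0, 0.32 at x = 0.8 and 0.40 at x = 1. In none of the fear-gain rows does CS+E−CS− fall.

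**3. Could a trial of this size declare such a shift?** Assume a two-sided 5% level and let d be the shift on CS+U vs CS+E in units of the SD of the within-patient difference.

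- Medication main effect, n = 80: Φ(d·√80 − 1.96). For d = 0.2, 0.3, 0.4, 0.5 this is 0.43, 0.77, 0.95, 0.99.
- Group-by-medication interaction, with the shift only in the dysregulated half (median split, about 40 against 40): Φ(d/√(2/40) − 1.96). For the same d this is 0.14, 0.27, 0.43, 0.61.
- A shift equal in both groups leaves the interaction unmoved and appears only as a medication main effect.

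**The case against.** The strongest reply is that the information is already in the plan. The two named contrasts add up to the missing one: (CS+U−CS+E) + (CS+E−CS−) = CS+U−CS−. Read together, they separate the explanations: true benefit moves them in opposite directions, while fear gain moves them the same way or leaves one flat. This stands. The gap is the and/or rule, which lets one be read without the other, rather than a missing measurement. A reader might infer that the trial cannot detect a strengthened fear memory; the documents do not support that.

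A reader might also infer that hydrocortisone would raise CS+U vs CS+E. That is not established. It needs proportional or CS+U-only strengthening, and an equal additive gain leaves the contrast unchanged. Nor do the main-effect probabilities describe the hypothesised test. The interaction is mimicked only if strengthening differs by HPA group. That case is not remote, since the trial itself expects the groups to respond differently to the drug, but the article does not show it.

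Third, section 2.6.2.1 declares fear memory a target of recall and leaves psychophysiological detail to Supplement S13, which is not shown. The safe statement is therefore that the article names no such contrast. That section also ties stronger extinction to smaller differential responses, which suits CS+E vs CS− but runs opposite to section 2.6.2.2 for CS+U vs CS+E. The two need reconciling, but that does not settle how the drug comparison will be read.

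Finally, it is tempting to call this a patient-safety issue. The task pairs geometric shapes with finger shocks in a proof-of-concept study, and nothing shown demonstrates that dosing hours after acquisition strengthens fear. The point concerns the validity of an interpretation.

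**Conclusion.** The concern holds in limited form. As written, a higher CS+U vs CS+E under hydrocortisone may be taken by itself as stronger extinction, although a stronger fear memory can produce the same shift. In the illustration the two are identical at +0.20. The conclusion rests on three things: same-day dosing after acquisition, the Abstract's general premise about emotional memories, and strengthening that is proportional or confined to CS+U.

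For the hypothesised interaction it also requires strengthening that differs between HPA groups. The chance of a misleading significant result is then 0.27 to 0.61 for assumed shifts of 0.3 to 0.5 SD in the dysregulated half. Otherwise the artefact is confined to the medication main effect. It merits a change of wording before analysis because it bears on the main question of part B, but it does not invalidate the design.

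**What to change.** In section 2.6.2.2, objectives 1 and 2:

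- Prespecify CS+U vs CS− at recall, by medication, group and context, as a specificity contrast.
- Replace and/or with a joint reading. A rise in CS+U vs CS+E is not interpreted as stronger extinction when CS+U vs CS− also rises, and CS+E vs CS− is always reported and interpreted beside it.
- Give CS+U vs CS− as an estimate with its confidence interval, since a non-significant result does not show that fear memory was unchanged.
- Report a rise in CS+U vs CS− as an unfavourable effect on fear memory.

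Do not make a fall in CS+E vs CS− an absolute condition for claiming benefit. Section 2.6.2.1 expects shock expectancy to be gone by the end of extinction, so CS+E may already lie near CS− under placebo and have little room to fall.

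The cost is wording only, because responses to all three stimuli are already recorded at recall. The small downside is that a result carried only by higher CS+U responding can no longer be claimed as an extinction benefit.
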